#### Sensitivity analysis

A sensitivity analysis will be conducted to assess for any potential bias in the analysis of the primary and secondary outcome.

Observation periods will be removed for the sensitivity analysis if there is any precipitation that lasts for more than 50% of the observation period i.e. an overall accumulated duration of 30 min or more (recorded by the observer). This is in line with recommendations from MOHAWk [33].

Analysis will be undertaken using SPSS version 23 or later.

### Power calculation

Given the lack of previous studies of the causal effects of urban street greening, it is difficult to estimate the plausible size of the effect that interventions will have on the outcomes. However, the interventions only target one known variable that can influence physical activity and wellbeing within the context of a broader complex ‘system’ [50]; therefore, the effects on the measured outcomes, particularly physical activity, are likely to be small.

To assess the power of the study, we conducted a power calculation of the primary outcome measure: counts per observation period (hour) of Take Notice behaviour in older adults. We used the approach suggested by Donner and Klar ([51], p.66) for calculating the sample size for a matched pair design: calculate the number of clusters required for a completely randomised cluster design, and then multiply that by one minus the correlation between the mean outcomes in the two groups. This suits our context because it allows us to account for multiple comparison groups for each intervention group. We used the means and standard deviations (SD) from the two sites in the feasibility study. We assumed that one site was the ‘comparison’ group (i.e. the intervention site at baseline) and the other site was the ‘intervention’ group (this site had two benches, more greenery and was thus more aesthetically appealing based on ratings using the NGST). For the SDs for each site, we used the 80% upper one-sided confidence limit of the SD to account for the possibility that the SD from the feasibility data may be an underestimate.

A power calculation showed that if we match four intervention sites and eight comparison sites (12 in total) and have eight observation periods per cluster, we will have 99% power (*p* = .05, two-tailed test) to detect a difference between 0.5 (SD = .77) counts per observation period of Take Notice behaviour in older adults in the control group and 1.6 (SD = 1.72) in the intervention group. This assumes the ICC is 0.02, *p* = .05, two-tailed test: this low ICC value has been used in previous studies that have evaluated homogeneous parks ([name], personal communication). This also assumes that the ‘comparison’ group and ‘intervention’ groups from the feasibility study accurately represent the comparison and intervention sites in the main study at follow-up. However, due to the lack of data from previous studies on changes in older adult’s Take Notice behaviours in urban street greening interventions, data from the feasibility data was the most suitable available data to inform the power calculation.

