#### Observation schedule and procedure

Informed by data from the feasibility study, observations will be conducted over 2 days, four times a day (weekdays only) at each time point, resulting in a total of eight observation periods for each site at each time point. Observations will be conducted at four set observation periods per day: morning (10-11 am), lunchtime (12-1 pm), afternoon (3-4 pm), and evening (5-6 pm). These times were found to capture the biggest variation in older adults’ activity across the day (Fig. 1), whilst also providing sufficient time for breaks and possible travel to other sites in between observation periods.

Observations for each intervention site and the two corresponding comparison sites will be spread over 2 weeks. This will provide a more robust assessment of activity over a longer period rather than observing activity during a single week. Observations will be counterbalanced to control for week, day of week and time of day. The observation schedule used for baseline data collection is displayed in Fig. 3; this schedule will be replicated at all follow-ups. Any missed observations (e.g. due to illness) will be rescheduled for the same day of the next available week.

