#### Main analysis

The analysis will estimate the effect of the intervention on the number of older adults using the site at each of the two time points, and the types of behaviours they engage in per observation period, compared to the two corresponding comparison sites. The analysis will control for known confounders including weather, day and time. The primary analysis will analyse data for older adults and a secondary analysis will analyse data for all adults using the same methods.

The primary outcome will be a count per observation period of Take Notice behaviour at 12 months. Take Notice behaviour is the primary outcome because the interventions are expected to improve the aesthetic quality of green space by providing visual information of value to users, thus causing more overt appreciation in the intervention sites. The secondary outcome will be the overall count of older adults per observation period. Additional exploratory analyses will assess a count per observation period separately for each physical activity level (Sedentary, Walking, Vigorous) and Connect behaviour.

For each outcome we will follow three steps. Firstly, using a dataset that only includes the baseline data, and is blinded to group allocation, we will build a regression model to examine the relationship between the baseline count outcome and the covariates (weather, day, time). The overall count of older adults per observation period will be used as an additional covariate when analysing each of the behaviours (i.e. Sedentary, Walking, Vigorous, Take Notice, Connect). We will consider this count outcome as either a poisson distribution, a zero-inflated poisson or a normal distribution. We will consider all these approaches, and we will choose the most suitable approach by seeing which model has the best fit, assessed using Akaike’s information criterion (AIC) and measures of over-dispersion. Secondly, once we have developed a suitable model with the baseline data, we will combine the pre- and post-intervention data together and apply the model from step one. Thirdly, we will add into the model Group (intervention or comparison) and Period (pre or post). The treatment effect will be the coefficient for the interaction of Group and Period. This is a form of Difference in Differences analysis [48, 49], adapted because we do not have a before and after measure at the level of the hour.

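### The 99% power applies to a follow-up-only comparison of two means with an unprinted matching correlation, not to the planned Group-by-Period interaction

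*Protocol article*

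**What the plan says.** The Power calculation section of the protocol article describes a matched-pair cluster method. It finds the number of clusters for an unmatched cluster design and then tells the reader to "multiply that by one minus the correlation between the mean outcomes in the two groups". The design entered is "if we match four intervention sites and eight comparison sites (12 in total"), with eight hourly observation periods per site, ICC 0.02 and two-sided alpha 0.05. The contrast is "to detect a difference between 0.5 (SD = .77) counts per observation period" "in the control group and 1.6 (SD = 1.72) in the intervention group". Both means come from the two feasibility sites and are assumed to represent comparison and intervention sites at follow-up. The SDs are 80% upper one-sided confidence limits. The claim for this design reads "and have eight observation periods per cluster, we will have 99% power". The value of the matching correlation is not among the printed assumptions.

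The Main analysis section sets the primary outcome as the Take Notice count per observation period at 12 months. Pre- and post-intervention data are combined, and "The treatment effect will be the coefficient for the interaction of Group and Period". The terms it names are weather, day, time, the overall count of older adults, Group and Period. No matched-set term is named. The section says that the difference-in-differences form was adapted because there is no before-and-after measure at the level of the hour.

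**The concern.** The powered test and the planned test differ. A follow-up comparison of two means has two sources of sampling noise; a Group-by-Period interaction has four, because the two baseline means are estimated too. Nothing in the power section accounts for the extra two. The method also takes a matching gain of unstated size, and the analysis names no term that would realise it.

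The figure matters for how the primary result is read. The Discussion lists the power calculation among the methodological improvements, and the power section itself expects small effects. The 99% is for a rise from 0.5 to 1.6, a ratio of 3.2. A null result set against 99% power would look like stronger evidence of no effect than the planned test can give.

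**Working it through.** **Inputs from the article.** Means 0.5 and 1.6 (difference 1.1); SDs 0.77 and 1.72; 4 and 8 sites; eight hours per site per time point (Observation schedule and procedure: "resulting in a total of eight observation periods for each site at each time point"), so 32 and 64 hours; ICC 0.02; two-sided alpha 0.05. Design effect = 1 + 7 × 0.02 = 1.14.

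**Step 1: the plan's own figure (follow-up only).**
- Each arm's own SD, no matching gain: SE = √[1.14 × (1.72²/32 + 0.77²/64)] = √[1.14 × (0.09245 + 0.00926)] = 0.3405. Ratio 1.1/0.3405 = 3.23; power 89.8%.
- SD pooled by sample size: √[(32 × 1.72² + 64 × 0.77²)/96] = 1.175; SE 0.272; ratio 4.05; power 98.2%.
- Treated as eight matched pairs (8 versus 8 sites): SE = √[1.14 × (1.72² + 0.77²)/64] = 0.2515; ratio 4.37; power 99.2%.
- Matching correlation needed for 99%: the ratio must be 1.960 + 2.326 = 4.286. With own SDs, 1 − (1.1/4.286)²/0.11595 = 0.43. With the two variances averaged (SD 1.33), it is 0.31.

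So 99% can be reached, but each of these routes is a follow-up-only contrast. Which one the authors took cannot be told from the text.

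**Step 2: the planned interaction.** Added assumptions: baseline 0.5 (SD 0.77) in both groups, SD 1.72 only in intervention sites at follow-up, no matching gain. The power section supports the baseline mean, since it equates its comparison value with an intervention site at baseline. The article prints no separate baseline SD.

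Variance = 1.72²/32 + 0.77²/64 + 0.77²/32 + 0.77²/64 = 0.09245 + 0.00926 + 0.01853 + 0.00926 = 0.1295.

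| Handling of ICC 0.02 | SE | Ratio | Normal | t, 10 df | t, 3 df |
|---|---|---|---|---|---|
| Stable site effect cancels (× 0.98) | 0.356 | 3.09 | 87% | 79% | 55% |
| Ignored | 0.360 | 3.06 | 86% | 79% | 55% |
| Acts afresh in each period (× 1.14) | 0.384 | 2.86 | 82% | 73% | 50% |

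**Step 3: the most favourable variance choice.** One residual SD pooled over the four cells is √[(32 × 1.72² + 160 × 0.77²)/192] = 0.994. With the ICC ignored, SE = 0.994 × √(2/32 + 2/64) = 0.304; ratio 3.62; power 95%. A simulation of over-dispersed counts with the stated means and SDs (ICC 0, 20,000 runs) gave 94% for the normal model on hours, 78% and 84% for Poisson with and without over-dispersion adjustment, 90% for a site-level t test and 54% for a matched-set t test. The 94-95% is flattered, because pooling understates the noise when the smaller arm has the larger SD. With these variances, the nominal 5% test would reject under no effect with probability 2 × [1 − Φ(1.96 × 0.304/0.360)], about 10%.

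**Step 4: if a matching correlation carried over.** Multiply the variances in Step 2 by one minus the correlation. At 0.3, normal-approximation power is 93-96%; at 0.43 it is 97-98%. Reaching 99% would need 1 − (1.1/4.286)²/variance, which is 0.48 with variance 0.98 × 0.1295 and 0.55 with 1.14 × 0.1295.

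**The case against.** Several points on the other side stand.

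- *No arithmetic slip is shown.* A reader might infer that 99% was miscalculated. Step 1 shows that it can be reproduced with a correlation of about 0.31-0.43, or as eight pairs. The defect is a mismatch between the powered and planned tests, plus one unreported input.
- *No single replacement figure follows from the article.* A reader might infer that the article's own inputs give the planned test 55-86% power. They do not. That range also needs a zero matching correlation, a baseline SD, an ICC structure and a choice of degrees of freedom, none of which is printed.
- *The 3-df figure of 50-55% should not set the low end.* It pays in degrees of freedom for analysing four matched sets while denying any gain from matching. If matched set is in the model, a gain may be available; if it is not, this is not the planned test.
- *A 10-df site-level t test is not what the article describes.* It describes a regression on hourly counts, and how clustering enters may be settled in a fuller analysis plan. The article does not say whether normal or t quantiles were used for the 99%.
- *Some choices are cautious.* The SDs are upper confidence limits, covariate adjustment may reduce residual variance, and the article admits that the feasibility contrast is an assumption and that effects are likely to be small.

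None of this makes 99% the power of the interaction. The cautious SDs are already in every figure above, and the effect of the covariates cannot be quantified from the article.

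**Conclusion.** The 99% describes a different test from the one that the article fixes for its primary outcome, and it cannot be checked because the matching correlation is not given. On the Step 2 assumptions, the interaction has about 82-87% power (normal) or 73-79% (site-level t, 10 df), and up to about 95% with a pooled residual SD. A correlation of 0.3-0.43 that carried over would raise the normal-approximation figures to about 93-98%.

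A reader might go further and conclude that the design cannot have 99% power even for this tripling. The article does not support that as a fact: with own SDs and the normal approximation, a carried-over correlation of roughly 0.48-0.55 would reach it. What can be said is that no such value is printed, no matched-set term is named that would use it, and no variant computed here, up to a correlation of 0.43, reaches 99%.

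**What to change.** In the Power calculation section:

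1. Withdraw 99% as the power of the planned test. If it is kept at all, label it as a follow-up-only comparison of two means.
2. Recompute power for the Group-by-Period interaction at 12 months under the model that will be used, with the variance of all four group-by-period means.
3. Claim a matching gain only if matched set is in that model.
4. Print the matching correlation, the baseline SD, how the ICC is handled across periods and the degrees of freedom, and give the resulting range instead of one figure.

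This changes text and one calculation. The stated power will probably look less favourable. The number of sites, the observation schedule and the data collection stay as they are. The model changes only if the authors choose to add a matched-set term.

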## Discussion

This natural experimental study permits a rare and valuable opportunity to evaluate the causal effects of ‘real life’ changes in four small urban green spaces, within a deprived neighbourhood in an understudied population (older adults) and setting (UK). The findings will be useful for policy- and decision-makers in GM, as well as other urban areas in the UK and elsewhere in Europe.

This study will provide important methodological contributions by addressing seven out of eight key methodological weaknesses identified in a recent review to reduce bias in natural experimental studies [24] based on MRC guidance [20]. Bias due to confounding is a particularly pervasive problem in natural experimental studies [20]. We reduced the risk of bias due to confounding by developing a rigorous approach to comparison site matching and using appropriate statistical analyses to control for important known potential confounders (e.g. weather). Strengths of our novel approach to comparison site matching include the use of several objective and subjective variables at different levels of the environment (neighbourhood and street level) and multiple comparison sites to increase the likelihood of finding balanced comparison groups. Other methodological improvements in the present study include a published study protocol with a priori analyses specified, pioneering a newly developed tool to objectively measure physical activity and other wellbeing-related behaviours, clear reporting of interventions in line with the TIDieR checklist and a power calculation.

There is a lack of evidence and understanding on what specific kinds of changes in urban green space produce which outcomes in different contexts [47] i.e. what works, for whom and in what circumstances? [52]. The present study will address this issue by formally measuring the specific environmental change (i.e. aesthetic quality) using a UK validated tool for measuring the quality of green space (NGST). Using an objective outcome measure that is directly measured within the environmental context of interest will enable us to more confidently attribute changes in outcomes to the environmental change. This study will therefore provide an accurate insight into the effects of urban street greening on older adults’ physical activity and wellbeing in a deprived urban neighbourhood in the UK i.e. helping to answer what works, for whom and in what circumstances.

Understanding the pathways underlying the potential link between changes in urban green space (exposure) and physical activity and wellbeing (outcome) is important from a theoretical point of view, but also in terms of translating evidence into intervention or policy change [53]. However, there has been limited consideration and measurement of how changes in urban green space may work to change behaviour, particularly physical activity, in existing studies to date [15]. We developed a logic model explaining how the interventions are expected to influence older adults’ physical activity and wellbeing. We will seek to conduct a qualitative process analysis testing this logic model in a separate sub-study.

This study will use a parallel-groups design with a binary distinction between exposed intervention and unexposed comparison groups. A common difficulty when using this type of design is finding equally matched comparison sites. However, this design is suitable for the present study because intervention sites are located on residential streets; a type of land-use frequently found across the majority of neighbourhoods, thus providing ample unexposed potential matches. An alternative type of comparison site that can be used in natural experimental studies involves graded measures of exposure [54], such as distance from the intervention, as recommended by MRC guidance [20]. However, the interventions in this study are small; it is therefore unlikely that there will be any meaningful variation in exposure outside of the intervention site and thus graded measures of exposure would be less suitable.

## Conclusion

This study permits a rare opportunity to carry out a natural experimental study in the ‘real world’ as part of a multi-sectoral interdisciplinary collaboration. This study will also demonstrate the feasibility of incorporating rigorous methodology into the challenging field of natural experimental studies. As a result, this study will produce unique robust evidence on the causal effect of changes to urban green space in the UK on physical activity and wellbeing, in a growing but understudied ageing population in the context of environmental interventions.

## Abbreviations

AIC: Akaike’s information criterion
ICC: Intraclass correlation coefficient
IMD: Index of multiple deprivation
LSOA: Lower layer super output area
MOHAWk: Method for Observing pHysical Activity and Wellbeing
MRC: Medical research council
NEF: New Economics Foundation
RCT: Randomised controlled trial
SD: Standard deviation
SOPARC: System for Observing Play and Recreation in Communities
UK: United Kingdom
US: United States
